#### Groups

In the intervention group, participants will first receive the 2-week *brisk-walking training*. In addition, the participants in this group will learn about Samsung Health and WhatsApp. Subsequently, the participants in this group will receive the 12-week *e-health* programme. The intervention period will last for 14 weeks.

In the control group, the participants will first the 2-week *brisk-walking training*. In addition, the participants in this group will learn how to use a physical activity logbook to record their physical activity performance. Subsequently, the participants in this group will receive the *conventional behavioural change intervention* programme for 12 weeks. Finally, the intervention period will last for 14 weeks.

In both groups, participants are free to participate in any other activities provided by the elderly community centres or other organizations. However, participants are prohibited to participate in other additional activities related to brisk-walking training provided by other organizations during the intervention period.

#### Criteria for discontinuing interventions

If actual or potential harms are identified, the trial steering team will report them to the advisory panel, which will decide to consider suspending or terminating the trials.

#### Intervention fidelity

Training will be provided for the interventionist following an intervention protocol checklist that covers the most important steps used in our pilot study by the trial steering team [6]. The interventionist will implement the intervention procedures (e.g. WhatsApp, face-to-face meetings) following the procedure checklist and record their procedures to comply with the intervention protocols. This will ensure that all of the BCTs are delivered as planned. All communication on WhatsApp and via telephones will be logged. The trial steering team will be added to all of the WhatsApp groups as silent participants. The trial steering team will check the WhatsApp communications of a randomly selected group and conduct weekly site visits to observe face-to-face physical activity counselling sessions at a randomly selected centre. These random checks will enable the trial steering team to monitor the interventions implemented by the interventionist and ensure that the interventions are delivered in compliance with the protocol. Regular research team meetings will be conducted to determine whether the interventionist has followed the intervention protocol.

#### Tailoring

The goals of the brisk walking exercise (e.g. time, intensity) will be determined by 1) autosuggestions from Samsung Health based on the participant’s performance in the last week, 2) the participants’ wishes, and 3) suggestions made by the human interventionist based on the participants’ baseline fitness. The goals will be reviewed weekly and progressively increased (i.e. safe weekly increase < 20%/week) based on the joint decisions between the interventionist and the participants until the participants attain the target (i.e. 150 min MVPA/week).

### Outcomes

Demographic data include age, gender, level of education, number of chronic illnesses, financial satisfaction, living arrangement, years of smartphone usage, and perceived ability to use a smartphone. Demographic data will be collected at T0 (i.e. week 0) only. The primary outcome is MVPA. The four secondary outcomes are cognitive frailty, cognitive function, physical function, and physical activity motivation. All outcome data will be collected at T0 (i.e. week 0), T1 (i.e. week 15), and T2 (i.e. week 41).

#### MVPA (primary outcome)

MVPA will be quantified in MVPA minutes measured by a wrist-worn ActiGraph GT3X + , which has good criterion validity in differentiating between MVPA and non-MVPA in older people compared with indirect calorimetry (sens = 0.836, spec = 0.894, AUC = 0.932, *p*< 0.001) [45]. An MVPA minute is defined as a minute in which the ActiGraph mounted on the right wrist records physical movement (i.e. vector magnitude) of above 4212.9 count/min [45]. Only at least 10 min of continuous MVPA will be counted as valid MVPA minutes because the World Health Organization advises that engaging in MVPA for 150 min per week has health benefits when each session lasts for > 10 min [17]. Physical activity will be quantified by valid MVPA minutes measured over 7 consecutive days, as a 7-day interval is sufficient to discern an individual’s pattern of physical activity and is a widely used standard in studies of physical activity [46]. Only MVPA minutes measured on valid days (i.e. ActiGraph wearing time > 10 h/day) for a valid period (i.e. valid days > 3) will be considered valid [47].

#### Cognitive frailty

Cognitive frailty will be measured by a previously validated instrument, which quantifies cognitive frailty by two components: frailty (i.e. robust, pre-frailty, frailty) and MCI (i.e. yes, no) [48]. Frailty will be measured using Fried Frailed Phenotype, which quantifies frailty based on five components: weight loss, exhaustion, low physical activity, slow gait and weakness [33]. FFP scores range from 0 to 5, with one point assigned for the presence of one component. A higher score indicates greater frailty. Those with 0, 1–2 or 3–5 points are classified as robust, pre-frailty or frailty, respectively MCI will be measured using the MoCA score by assigning “yes” to the score ≤ 25 and “no” to the score > 25 [49]. The variable has six levels from level 1 at “no cognitive frailty” (i.e. robust without MCI) to level 6 at “cognitive frailty” (i.e. frailty with MCI). A higher score indicates a greater level of cognitive frailty.

#### Cognitive function

Cognitive function will be measured using MoCA [49], which comprises 30 dichotomous items. One point will be assigned to one correct answer. The total score ranges from 0 to 30. A higher score indicates a higher level of cognitive function. MoCA has strong correlations with other cognitive screening instruments, including Mini-Mental State Examination (*r* = 0.90) and Saint Louis Mental Status Examination (*r*= 0.83) [50]. MoCA also has good validity in detecting MCI (sensitivity = 0.90, specificity = 1.00) [49].

#### Physical function

Walking speed and functional fitness will be measured as forms of physical function. Walking speed will be measured by the Timed Up-and-Go test, which quantifies the total time needed for a participant to stand up from a chair, walk a 3-m distance, walk back to the chair, and sit down [51]. Functional fitness will be measured by the 30-s Chair Stand Test, which measures the number of stands a person can complete in 30 s [52].

#### Physical activity motivation

The Revised Motivation for Physical Activity Measure (RMPAM) will be used to measure physical activity motivation. RMPAM comprises 30 7-point items, each of which has five subscales with a total score ranging from 30 to 210. A higher score indicates greater motivation to perform physical activity [53].

### Participant timeline

As shown in Table 2 and Fig. 1, potential participants will be enrolled on the study in the phase of enrolment. The potential participants will be screened for eligibility. Eligible participants will be invited to sign the written informed consent after being explained the study details. After the enrolment phase, the pre-treatment assessment (T0, i.e. week 0) will commence. Demographic and outcome data will be collected. After that, participants will be randomly allocated to either the intervention or control group. Then, the interventions will commence. In the week immediately after the intervention (T1, i.e. week 15), the post-treatment assessment will commence and outcome data will be collected. Data of all outcome variables will be collected once again in the 6-month (i.e. 26 weeks) follow-up period (T2, i.e. week 41).

**Table 2 Tab2:** Schedule of enrolment, intervention, and assessments (SPIRIT-Figure)

Timepoint	Enrolment	Pre-treatment assessment	Allocation	Intervention	Post-treatment assessment	6-month follow-up
		T0			T1	T2
Enrolment						
Eligibility screen	x					
Informed consent	x					
Group allocation			x			
Interventions						
E-health				x		
CBCI				x		
Data collection						
Demographic		x				
Outcome						
MVPA		x			x	x
Cognitive frailty		x			x	x
Cognitive function		x			x	x
Physical function		x			x	x
Physical activity motivation		x			x	x

**Fig. 1 Fig1:**
[figure not shown]
Legend: T0: Baseline for pre-treatment assessment (i.e. week 0), T1: The week immediately after the intervention (i.e. week 15), T2: The week 6 months after the completion of the intervention (i.e. week 41)

### Sample size

We adopt a priori power analysis using the Web-based software GLIMMPSE and employ a general linear mixed model [54]. We set the level of significance at 0.05, the power at 0.9, the number of repeated measures at 3 (i.e. T0, T1, T2), the number of groups at 2 (i.e. the intervention and control groups) and the allocation ratio between the two groups at 1:1. To estimate the effects, we estimate the immediate effect of the intervention according to the effect on the primary outcome compared between two groups with the same interventions (i.e. e-health vs conventional behavioural change intervention) as reported in the pilot study of this project [55]. We assume the effects to be sustained until the 6-month follow-up. We estimate that the sample size is 132. We assume a cumulative drop-up rate of 18.1% at T1 and T2 [56]. The total sample size estimated is 184 participants, with 92 participants in each group.

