**Methods:**

This study employs a single-blinded, two-parallel-group, non-inferiority, randomized controlled trial design with a 1:1 group allocation ratio. Eligible participants are aged 60 years or above, have cognitive frailty and physical inactivity, and possess a smartphone for more than six months. The study will be conducted in community settings. In the intervention group, participants will receive a 2-week brisk-walking training followed by a 12-week e-health intervention. In the control group, participants will receive a 2-week brisk-walking training followed by a 12-week conventional behavioural change intervention. The primary outcome is minutes of moderate-to-vigorous physical activity (MVPA). This study aims to recruit a total of 184 participants. Generalized estimating equations (GEE) will be used to examine the effects of the intervention.

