Conventionally, a range of behavioural change techniques, standardized by the Coventry, Aberdeen, and London – Refined (CALO-RE) taxonomy (e.g. goal-setting, self-monitoring) and delivered by human interventionists, have been used to promote physical activity [22]. However, the conventional behavioural change interventions that have proven to be effective with younger people are less effective with older people [23]. E-health provides an alternative delivery method to conventional behavioural change methods delivered by human interventionists [24]. E-health uses persuasive technology methods delivered by computer interventionists that potentially enhance behavioural change effects [25]. Systematic reviews showed that e-health technologies increase physical activity in older people with a large effect [26–30]. Albeit the fact that e-health can more effectively promote desirable behaviours (e.g. MVPA), its effects are unknown in the context of vulnerable population (i.e. older people with cognitive frailty) and sustainability, and in comparison with conventional behavioural change interventions.

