### Trial design

This study employs a single-blinded, two-parallel-group, non-inferiority, randomized controlled trial.

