### Statistical methods

Demographic and outcome data at baseline will be reported either as means with standard deviation or as frequencies with percentages based on their level of measurement. Generalized estimating equations (GEE) will be used to separately test the hypotheses on the five outcomes, which are the dependent variables (i.e. MVPA, cognitive frailty, cognitive function, physical function, and physical activity motivation). The independent variables will be the same across all GEEs: group (two categories: intervention and control groups), timepoint (three categories: T0, T1, T2), and group x timepoint. The primary interpretation of the results will be based on the analysis based on the intention-to-treat principle without adjusting for possible covariates [60, 61]. Sensitivity analyses will be conducted and reported to compare the results of different methods of analysis, such as intention-to-treat and per-protocol analyses [62]. The level of significance will be set at 0.05. Missing data will be managed following Jakobsen’s algorithm according to the missing pattern with various methods (e.g. no imputation, multiple imputations) [63].

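### The trial is declared non-inferiority, but the sample size and primary test described are for detecting a difference and use no margin

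*Protocol article*

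**What the plan says.** The Trial design section states: "This study employs a single-blinded, two-parallel-group, non-inferiority, randomized controlled trial". The Methods paragraph of the Abstract gives the same label: "single-blinded, two-parallel-group, non-inferiority, randomized controlled trial design with a 1:1 group allocation ratio". Non-inferiority is mentioned nowhere else in the article, and no margin is given.

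The Sample size section begins "We set the level of significance at 0.05, the power at 0.9, the number of repeated measures at 3", then adds two groups and 1:1 allocation. For the effect it says "we estimate the immediate effect of the intervention according to the effect on the primary outcome compared between two groups with the same interventions", meaning e-health against the conventional intervention in the pilot, and it continues: "We assume the effects to be sustained until the 6-month follow-up". The result is 132, raised to 184 (92 per group) for dropout.

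The Statistical methods section fits GEE models with group, timepoint and their interaction. On the level it says: "The level of significance will be set at 0.05". On the analysis set it says: "The primary interpretation of the results will be based on the analysis based on the intention-to-treat principle without adjusting for possible covariates". Per-protocol analysis is listed among the sensitivity analyses. The Objectives section says only that the two interventions will be compared.

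**The concern.** A non-inferiority trial rests on a margin. The margin defines the null hypothesis, enters the sample size, and is what the confidence limit is judged against. Here the label is declared, but the calculation and the test are built around a difference between the arms. A later analysis plan could add a margin, but it could not make 132 a number that was derived from one. The mismatch therefore lies in the text itself and is not detail left out of a condensed article.

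What is at stake is how the main result may be read. Under a non-inferiority label, a non-significant interaction invites the conclusion that e-health is no worse, and the plan has no rule that prevents this. Contamination within a centre and low attendance, both of which the protocol anticipates, can make the arms look alike and so make a non-significant result more likely.

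**Working it through.** **Inputs from the Sample size section.** Level 0.05 (sidedness not stated), power 0.90, 1:1 allocation, three repeated measures, 132 before dropout, 184 after. The pilot effect, its standard deviation (SD) and the repeated-measures correlation are not given, so 132 cannot be reproduced.

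**What the listed inputs can yield.** They contain an assumed difference between the arms and no margin. The 90% is therefore the probability of detecting that difference.

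**Scenario in units of E.** Assumption: one contrast, normal approximation, two-sided 0.05. Let E be the size of the effect detected with 90% power. Then E divided by its standard error is 1.960 + 1.282 = 3.2415 (unrounded quantiles).

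*Non-significance when e-health is truly worse by fE.* P = 1 − [Φ(3.2415f − 1.96) + Φ(−3.2415f − 1.96)]
- f = 0.25: 0.872
- f = 0.5: 0.633

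The group-by-time interaction over three timepoints has 2 degrees of freedom. Treating it as a 2-df test that also has 90% power at E gives about 0.89 and 0.66, so the message is unchanged.

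*Non-inferiority power when the arms are truly equal, one-sided 0.025, margin fE.* Power = Φ(3.2415f − 1.96)
- f = 0.5: 0.367
- f = 0.67: 0.584
- f = 1: 0.900

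*Non-inferiority power when e-health is truly better by tE, margin mE.* Power = Φ(3.2415(t + m) − 1.96)
- t = 1, m = 0.1: 0.946
- t = 1, m = 0.5: 0.998
- t = 0.5, m = 0.5: 0.900

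**Rough scale in SD units.** Assumption: a simple comparison of two means, ignoring the repeated measures. With 66 per group, E = 3.2415 × √(2/66) = 0.56 SD. If the 0.05 is one-sided, the corresponding figure is 0.51 SD.

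Power for non-inferiority if the arms are truly equal, one-sided 0.025, is Φ(margin/√(2/n) − 1.96):

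| Assumed margin | n = 66 per group | n = 92 per group |
|---|---|---|
| 0.2 SD | 21% | 27% |
| 0.3 SD | 41% | 53% |
| 0.4 SD | 63% | 77% |
| 0.5 SD | 82% | 92% |

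The margins in this table are assumptions that show the range. None comes from the protocol.

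**The case against.** The best defence has several parts.

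- **An expected difference may enter a non-inferiority calculation.** This is true. If the pilot effect favours e-health and holds, power exceeds 90% for any positive margin. However, the direction of the pilot effect is not stated, and the calculation would still need a margin, of which the Sample size section shows no trace.
- **The GEE yields a confidence interval that can be set against a margin, and a significant result favouring e-health would itself exclude inferiority.** Both statements are correct. A reader might infer that no result of this trial could speak to non-inferiority, and that goes too far. What is missing is a prespecified margin-based conclusion, and a non-significant result cannot supply it. The protocol does not say that non-significance will be read that way; the risk comes from the label.
- **The 0.05 is not stated to be two-sided.** This stands. The two-sided reading is an assumption of the scenario.

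Three further inferences are tempting but not supported.

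- **That a primary intention-to-treat analysis marks a superiority trial.** It is not specific to superiority. Per-protocol analyses are planned, and the Data collection and management section provides for outcomes at T1 and T2 from participants who discontinue or deviate.
- **That the comparator is too weak for a non-inferiority claim.** The Background says "the conventional behavioural change interventions that have proven to be effective with younger people are less effective with older people". That compares older with younger people and does not call the comparator ineffective. The section on the conventional intervention reports favourable pilot results for it, including on MVPA.
- **That T1 alone must be the deciding contrast.** The Objectives pair immediate with sustained effects, so this would be a preference and not a correction.

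**Conclusion.** The point holds in this form: the declared design is non-inferiority, while the described sample size and test address a difference, with no margin in either. The stated 90% power does not apply to excluding inferiority.

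The size of the gap can be shown only as a scenario. If the arms are truly equal, a margin of half the detectable effect would have about 37% power instead of 90%, and a true deficit of that same size would go undetected about 63% of the time. These figures assume a single two-sided 0.05 contrast and the stated true differences. They are not properties of the planned repeated-measures test, whose effect, SD and correlation are not given. The mismatch itself depends on none of these assumptions. It should be corrected because the primary conclusion turns on it.

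**What to change.** Reconcile the label with the calculation before any outcome comparison, and so before the first of the interim analyses mentioned under Monitoring. There are two coherent routes.

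**(a) Declare a superiority comparison.** Remove the non-inferiority label from the Abstract, the Trial design section and the registry entry where it appears. State that a non-significant result will not be read as non-inferiority. This matches the existing sizing and test and needs no extra participants.

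**(b) Keep non-inferiority.** State a justified margin in MVPA minutes per week. Conclude non-inferiority only if the lower confidence limit for e-health minus conventional lies above minus the margin, and fix the confidence level. Report the per-protocol result alongside intention-to-treat. Restate the power for that margin at the planned number of participants, with the assumed true difference and SD.

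The article does not settle which question is intended, so the choice is the investigators'. Route (a) costs protocol and registry wording but changes the declared hypothesis, and it should be recorded as such. Route (b) costs the same wording plus a stated power that may be less favourable than 90%.

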## Discussion

Older people with cognitive frailty are potentially treatable to prevent further adverse health outcomes, the policymakers should put cognitive frailty, this relatively new health marker, a priority to treat in primary healthcare settings. E-health through smartphones is innovative which has great potential in developing effective interventions to promote health behaviours (e.g. physical activity) in older people with cognitive frailty and other health concerns (e.g. dementia) [44, 65]. This e-health brisk walking intervention may provide effective interventions to promote cognitive health prevention and preservation in primary healthcare settings. This project is innovative in fostering collaboration between academic and community settings (e.g. elderly community centres) where used to provide social and recreational activities, to provide potentially effective primary health promotion services. The project will launch an e-health intervention in several community centres for older people. Although there will only be approximately 192 participants in the study, we will continue to promote the adoption of the intervention in different community centres during and after the completion of the proposed study. A training package with written and video materials will be produced to facilitate the adoption of the intervention by other unparticipated elderly community centres. If the intervention proves effective in reducing cognitive frailty, the health of older people is expected to improve as well. Older people will benefit from living more independent lives, having fewer chronic diseases (e.g. dementia) and having better functionality (e.g. better mobility).

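### The sample size of 184 does not follow from 132 and 18.1% dropout on either reading of that rate, and the Discussion gives a conflicting figure of about 192

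*Protocol article*

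**What the plan says.** The sample size section describes an a priori calculation for a general linear mixed model with three repeated measures and two groups: "We set the level of significance at 0.05, the power at 0.9", with "the allocation ratio between the two groups at 1:1". The result before any allowance for loss is given as "We estimate that the sample size is 132". The allowance follows: "We assume a cumulative drop-up rate of 18.1% at T1 and T2" (evidently the dropout rate). The section then concludes: "The total sample size estimated is 184 participants, with 92 participants in each group".

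The abstract repeats the target: "This study aims to recruit a total of 184 participants". The Discussion, in remarks on wider adoption of the intervention, has a different number: "Although there will only be approximately 192 participants in the study".

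The article does not show the inflation formula. It also does not say whether 18.1% is the loss accumulated by T2 or the loss at each of the two follow-up assessments.

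**The concern.** An article may leave out the inflation formula. This one prints both the inputs and the result, so a reader can check whether one follows from the other, and it does not. The stated 90% power belongs to 132 participants. The reader therefore cannot tell whether 184 recruits protect that number, exceed it or fall short of it, because this turns on an undefined rate and a formula that neither reading supports.

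Separately, a document that gives both 184 and about 192 leaves unclear which figure later reports should use to judge whether recruitment met its target.

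**Working it through.** **Inputs.** From the sample size section: n = 132 before loss, d = 0.181, stated total 184 (92 per group), power 0.90, significance level 0.05 (sidedness not given). From the abstract: 184. From the Discussion: about 192. There are two post-baseline assessments, T1 (week 15) and T2 (week 41). The 132 itself cannot be checked, because the effect size, standard deviation and correlations are not printed.

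**Reproducing 184.**
- Multiply up once: 132 × 1.181 = 155.9. No match.
- Multiply up additively for two visits: 132 × (1 + 2 × 0.181) = 179.8. Close, but no match.
- Multiply up twice: 132 × 1.181² = 132 × 1.394761 = 184.1. Match. Per group, 66 × 1.394761 = 92.05, which also matches 92.

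**What retaining 132 would need.** To keep n after a loss fraction d, N = n/(1 − d).
- 18.1% is the total loss by T2: 132/0.819 = 161.2, so 162 (81 per group). The stated 184 is 22 above this.
- 18.1% is lost at each of T1 and T2: 132/0.819² = 132/0.670761 = 196.8, so 197, or 198 with equal groups (66/0.670761 = 98.4, so 99 per group). The stated 184 is 14 below 198.
- Reading backwards, going from 184 to 132 means a total loss of 1 − 132/184 = 28.3%, a rate that appears nowhere.

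**The 192.** It equals neither 162 nor 197–198. Mixing the two formulas (162 × 1.181 = 191.3) comes close but is not a coherent calculation.

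**What 184 delivers.** Power is approximated by scaling from 90% at 132: power = Φ[(1.960 + 1.282) × √(m/132) − 1.960], where m is the number of completers and the test is taken as two-sided at 0.05.

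| Meaning of 18.1% | Cumulative loss | Completers from 184 | Approximate power |
|---|---|---|---|
| Total by T2 | 18.1% | 184 × 0.819 = 150.7 | Φ(3.463 − 1.960) = 0.934 |
| At each of T1 and T2 | 1 − 0.670761 = 32.9% | 184 × 0.670761 = 123.4 | Φ(3.134 − 1.960) = 0.880 |

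Sidedness hardly matters. With a one-sided 0.05 test the sum of quantiles is 1.645 + 1.282 = 2.926, and the two powers become Φ(3.127 − 1.645) = 0.931 and Φ(2.830 − 1.645) = 0.882.

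**The case against.** The strongest objection is that little hangs on this. The abstract and the sample size section agree on 184. The 192 is prefaced as approximate and sits in a sentence about adoption. Taken literally, a cumulative rate of 18.1% leaves the trial with more completers than it needs. Even on the less favourable reading, power moves by only about two points. That stands as an argument about severity. It does not remove the mismatch, because 184 is not what the printed inputs give on either reading.

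A reader might infer that the plan leaves the trial short, with about 123 completers instead of 132. The documents do not support this as a plain statement. It holds only if 18.1% is lost at each visit, while the text calls the rate cumulative; read that way, about 151 remain.

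A reader might also treat the twice-applied multiplication as established. It is an inference: the match on both the total and the per-group figure is striking, but no formula is shown, and the source cited for the rate is not available here.

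The completers-only power figures can also be challenged. The statistical methods section plans GEE over all three time points under intention-to-treat, with missing data handled by methods that include multiple imputation. The data collection section says outcomes will still be collected from people who discontinue the intervention. On the per-visit reading about 151 people (184 × 0.819) would still have T1 data. Using those partial data would make the loss of power smaller than the approximation shows.

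Finally, one might add invalid ActiGraph wear as a further loss not provided for. The article does not say whether 18.1% includes it, so that cannot be claimed.

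**Conclusion.** The point holds as an arithmetic inconsistency. The stated total of 184 differs from what 132 and 18.1% require by +22 (total loss) or −14 (loss per visit, equal groups), and the Discussion's 192 conflicts with the 184 given elsewhere. Neither conclusion depends on how 184 was produced.

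The practical effect is small and its direction is open. Against the stated 90%, power would be about 93% if 18.1% is the total loss, and about 88% if it is lost at each visit. Those figures assume 90% power at 132, a normal approximation with a two-sided 0.05 test, and information from completers only. Severity is minor to moderate: the basis for the primary sample size cannot be reproduced as printed, but no analysis or design element has to change.

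**What to change.** Define 18.1% as either the total loss by T2 or the loss at each follow-up visit, and show the calculation. Keep N = 184 as the recruitment target, and present it as the chosen number, not as the result of inflating 132. Then restate what goes with it:

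- Total loss: 18.1% cumulative, about 151 completers, power about 93%, with a note that 162 would have been enough to retain 132.
- Loss per visit: 32.9% cumulative, about 123 completers, power about 88% on a completers-only basis, with a note that 197 (198 with equal groups) would have been needed to retain 132.

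The power is better rerun in the original software with the pilot inputs; the values here are approximations. Change the Discussion's figure of about 192 to 184, so that it agrees with the abstract and the sample size section.

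The cost is a text correction in two sections. No extra participants are needed. On the per-visit reading the stated power becomes slightly less favourable.
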